### The control groups

Participants in the non-specific acupoint group will follow the exact same procedure as the treatment group.

Participants in the blank control group will be instructed to maintain their regular daily routines, enabling the isolated effect of ARAT to be analyzed. If the results of the study are favorable, participants in the two control groups will be offered the opportunity to receive ARAT free of charge.

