### Sample size

The primary outcome measure is Total Nasal Symptom Score (TNSS). As there are no existing studies on ARAT, a new type of acupressure, the sample size calculation was based on a pilot study of ARAT for PAR that utilized the same outcome measure (Table 2). Using these results and considering the study's objectives, the sample sizes for the ARAT group and the non-specific acupoints group were separately calculated for comparison with the blank control group. The calculations were performed with α=0.05 and β=0.1, and the maximum sample size for each group was determined to be 33 cases using PASS11.0 (NCSS, LLC. Kaysville, UT, USA) software. Accounting for a potential 10% dropout rate, a total sample size of 111 participants will be recruited for this trial, with 37 participants allocated to each group.

**Table 2 Tab2:** Pilot study of ARAT for perennial allergic rhinitis

	**the ARAT group**	**the non-specific acupoints group**	**the blank control group**

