### Blinding

Considering the significant contrast in content between the treatment and control groups and the lack of an impact on the therapy's final effects, blinding procedures will not be applied in this trial. Therefore, both the investigators and the participants will be aware of the type of intervention during the clinical trials.

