#### The treatment group (The ARAT group)

At the start of the intervention, the therapists will provide individualized, face-to-face instructions and training on ARAT techniques to each participant in the treatment group.

A video will be created that that includes lectures, demonstrations, and practice sessions conducted by nurses and therapists, demonstrating the correct acupressure techniques. This video will be uploaded to the app for participants to access.

Participants in the treatment group will perform self-administered acupressure on the designated acupoints for approximately 10 minutes every night, either after bathing or before sleeping. Participants will undergo 20 sessions treatment for 4 weeks. They will apply pressure to each acupoint 60 times, completing the entire session within the allocated time. Participants should apply sufficient pressure to experience a sensation of pressure, warmth, and slight soreness. The app will contain the video, which will be distributed to each participant. Participants will be asked to check-in at the start and end of each session.

Throughout the treatment period, participants will undergo weekly video-call check-ins to monitor their acupressure technique. Post-intervention assessments will be conducted at the second and fourth week after the intervention using the same questionnaire used in the pre-intervention assessment.

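### ARAT versus blank control estimates the whole self-acupressure package, not the isolated effect of ARAT; only the non-specific acupoints arm is matched on contact

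*Protocol article*

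**What the plan says.** Under The control groups, the protocol states that blank-arm participants are told to carry on as usual, "enabling the isolated effect of ARAT to be analyzed". The isolation claim is thus attached to the blank arm.

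Under The treatment group, "the therapists will provide individualized, face-to-face instructions and training on ARAT techniques to each participant in the treatment group". A technique video is supplied through the app. "Participants will be asked to check-in at the start and end of each session", and "participants will undergo weekly video-call check-ins to monitor their acupressure technique".

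For the other acupressure arm, "Participants in the non-specific acupoint group will follow the exact same procedure as the treatment group". The Intervention section lists only the health education video and the study medication as common to all three arms.

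Under Blinding, "both the investigators and the participants will be aware of the type of intervention during the clinical trials". The primary outcome, TNSS, is scored by the participants themselves. Under Sample size, the numbers for the two acupressure arms "were separately calculated for comparison with the blank control group".

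**The concern.** A control isolates a treatment effect only if the arms differ in that treatment and nothing else that can move the outcome. Here the blank arm differs from ARAT in the points pressed, the act of pressing, the nightly routine, the contact with therapists and staff, and what participants expect. Every participant knows the allocation and rates his or her own symptoms.

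What is at stake is the interpretation of a main comparison. A favourable ARAT-versus-blank result read in the protocol's own terms would credit ARAT alone with a difference to which contact and expectation may have contributed. The trial has an arm better suited to that claim, but neither the isolation sentence nor the sample-size paragraph uses it for that purpose.

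**Working it through.** **1. What differs between the arms**

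| Component | ARAT | Non-specific | Blank |
|---|---|---|---|
| Education video, study medication | yes | yes | yes |
| Individual training, technique video | yes | yes | not described |
| Session check-ins, weekly technique calls | yes | yes | not described |
| Points pressed | ARAT set | other true acupoints | none |
| Knows allocation, self-rates TNSS | yes | yes | yes |

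The blank arm's lack of training and calls is inferred. Both are described only for acupressure, and both concern its technique.

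Write P_A and P_N for the effects of pressing the two sets of points, C for contact and routine, and E_A and E_N for expectation relative to blank. If these add up:

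- ARAT − blank = P_A + C + E_A
- non-specific − blank = P_N + C + E_N
- ARAT − non-specific = (P_A − P_N) + (E_A − E_N)

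Only the third contrast removes C. None removes expectation with certainty.

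**2. The plan's own figure.** 33/(1 − 0.10) = 36.7, rounded up to 37, and 3 × 37 = 111, so the dropout step reproduces. The 33 cannot be the larger of the two described calculations: non-specific versus blank on pilot post scores (difference 0.2, SD 1.756) needs 2 × (1.960 + 1.282)² × 1.756²/0.2² ≈ 1,621 per group. That is a separate matter, and nothing below depends on it.

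**3. Pilot inputs (Table 2, TNSS, pre then post)**

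- ARAT 9.7 (SD 2.2), 5.1 (SD 1.7): change 4.6
- Non-specific 9.5 (SD 2.0), 7.1 (SD 1.9): change 2.4
- Blank 10.1 (SD 1.7), 7.3 (SD 1.6): change 2.8

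The abstract makes change in TNSS the primary outcome. The SD of change is √(s₁² + s₂² − 2r·s₁·s₂). The correlation r is not given, so 0 to 0.7 is assumed. SDs are pooled over two arms as √((s_a² + s_b²)/2). Power is for a two-sided t-test at 0.05 with noncentrality d/(SD × √(2/n)).

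**4. How often context alone would give a significant ARAT-versus-blank result.** Set the specific effect to zero and assume a contextual benefit d.

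- Post scores, SD = √((1.7² + 1.6²)/2) = 1.65. For d = 0.5 the rate is 0.228 (n = 33) and 0.251 (n = 37). For d = 1.0 it is 0.679 and 0.729.
- Change scores, n = 33, SD 2.57 (r = 0) to 1.44 (r = 0.7). For d = 0.5 the rate is 0.122 to 0.285. For d = 1.0 it is 0.344 to 0.794.

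**5. Power of the contact-matched contrast, ARAT versus non-specific, n = 33**

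- Post scores: difference 2.0, SD √((1.7² + 1.9²)/2) = 1.80, power 0.993.
- Change scores: difference 4.6 − 2.4 = 2.2. At r = 0 the SD is √((7.73 + 7.61)/2) = 2.77, noncentrality 2.2/(2.77 × 0.246) = 3.23, power 0.888. At r = 0.7 the SD is 1.55 and power exceeds 0.99.
- For comparison, ARAT versus blank on change (difference 1.8) has power 0.801 at r = 0 and over 0.99 at r = 0.7.

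At r = 0, 33 per arm falls just short of the planned 90%, and 37 per arm gives 0.921.

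**6. What the pilot says about context.** Non-specific is 0.2 better than blank on post scores but 0.4 worse on change (2.4 versus 2.8). The pilot size is not stated. In this trial the 95% half-width for that difference on post scores would be 1.96 × 1.756 × √(2/n): 0.85 at n = 33 and 0.80 at n = 37.

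**The case against.** The best defence is that ARAT is introduced as a taught, self-administered treatment approach, so isolating its effect may only mean separating it from the shared drug and education. An add-on control largely does that. This softens the charge, but the contrast still includes trainer contact and expectation, and the sentence does not say so.

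Second, the design already contains the remedy: a procedure-matched arm, planned pairwise comparisons, and a questionnaire on expectation and credibility. That stands. A reader might infer that the trial cannot address a specific effect at all. The documents do not support that; the fault is that the claim is attached to the wrong contrast.

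Third, the pilot gives no sign of a contextual benefit. That also stands, so the rates in step 4 of the working are illustrations, not predictions. They do not restore the claim, because the pilot size is unknown and the new trial could not exclude a modest effect.

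Two further inferences go too far. One is that non-specific versus blank measures the contextual effect. The non-specific points are true acupoints, and the Discussion says that their own therapeutic effect still has to be determined. The other is that ARAT versus non-specific isolates the points completely. Participants are unblinded, so expectation may differ between the two acupressure arms as well.

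**Conclusion.** The point holds as a fault of stated interpretation. The blank arm does not enable an isolated effect of ARAT to be analyzed; it gives the effect of the package over routine care. The data remain usable and the design need not change.

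The possible size depends on an assumed contextual effect. At 0.5 and 1.0 TNSS points, false attribution would occur at about 0.23 to 0.25 and 0.68 to 0.73 on post scores (33 to 37 per arm). On change scores at 33 per arm it would occur at 0.12 to 0.29 and 0.34 to 0.79. All of these exceed the nominal 0.05.

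A reader might also infer that the protocol must place ARAT versus non-specific first in a formal hierarchy. The document fixes no order of comparisons, and that is commonly left to the analysis plan. What is needed here is that each contrast be described as what it estimates.

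**What to change.** Replace the isolated-effect clause under The control groups with three statements:

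- ARAT versus blank estimates the effect of the self-acupressure package, including training, check-ins, calls and expectation, over routine care.
- Any claim about the specific ARAT acupoints rests on ARAT versus non-specific acupoints, the only contact-matched contrast. Participants are unblinded, so expectation may still differ.
- Non-specific versus blank estimates context plus any effect of pressing those true acupoints.

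Add the ARAT-versus-non-specific figure to Sample size: on pilot change scores (difference 2.2), 33 per arm gives about 89% to over 99% power for assumed correlations of 0 to 0.7, and 99% on post scores.

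No extra patients or visits are needed. The costs are that the specific-effect claim then rests on a stricter contrast, and that the change must be notified to the ethics committee and the registry, with recruitment already open since July 1, 2023.

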### Outcomes

This clinical trial will assess primary and secondary outcome measures. The outcomes will be compared between the groups at baseline, at the end of the treatment period, and at the end of the follow-up period. The recruitment, intervention, and assessment schedule for the randomized controlled trial is presented in Table 1.

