**Discussion:**

This study may produce a new acupressure treatment prescription that is easy to learn, more targeted, and adaptable. This trial represents the first clinical investigation comparing ARAT treatment for PAR with the non-specific acupoints group and blank control group. Our data is expected to provide evidence demonstrating the safety and efficacy of ARAT for PAR patients, while also exploring the functional mechanism underlying ARAT treatment, moreover, the results offer valuable insights for healthcare professionals in managing PAR symptoms.

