#### Primary outcome measures

The primary outcome measure for this clinical trial will be TNSS. TNSS evaluates four nasal symptoms: nasal obstruction, running nose, sneezing, and nasal itch. Participants will self-assess and record the severity of their symptoms using a four-point scale (0 = no symptoms; 1 = mild symptoms; 2 = moderate symptoms; 3 = severe symptoms) [3, 28]. TNSS scores range from 0 to 12, , with lower scores indicating milder nasal symptoms. Previous studies [29, 30] have utilized the TNSS as an assessment tool.

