Additionally, the treatment mechanism of ARAT will be explored in this trial. Nasal secretions from eligible participants will be collected by research nurses at the beginning and end of the treatment. These biological specimens will be centrifuged and stored in the Biological Resource Center of SCCGZUCM for molecular analysis. Cytokines such as interleukin-5 (IL5), IL13, thymic stromal lymphopoietin (TSLP), and interferon-gamma (IFN-γ) will be detected using the enzyme-linked immunosorbent assay (ELISA) method.

Among these outcome measures, TNSS and RQLQs will be assessed at the beginning, middle, and end of treatment period, as well as during the follow-up period at weeks 4, 8, and 12. The other measures will be assessed at the beginning and end of the treatment period.

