### Statistical analysis

Qualified statisticians who are blinded to the treatment group data will perform all efficacy and safety analyses following the intention-to-treat (ITT) principle using SPSS 20.0 (IBM SPSS Inc., Armonk, New York, USA). Missing values will be estimated using the last recorded data. A significance level of α= 0.05 will be considered statistically significant. The median, minimum, and maximum values will be used to express measured data. Group comparisons will be analyzed using Analysis of Variance (ANOVA) and pairwise comparisons (rank-sum test for univariate variance). Count data will be expressed as composition ratios or rates, and comparisons between groups will use the χ2 test for efficiency and rank-sum test for efficiency and rank-sum test for ranked data.

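### TNSS has no named primary time or contrast, and it is compared at two post-baseline times at 0.05 with no stated order, gating or adjustment

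*Protocol article*

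**What the plan says.** All references are to the protocol article.

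- Primary outcome measures: "The primary outcome measure for this clinical trial will be TNSS". No time is attached. The abstract speaks of the change in TNSS, also without a time.
- Outcomes: "The outcomes will be compared between the groups at baseline, at the end of the treatment period, and at the end of the follow-up" period. This gives two post-baseline comparison times.
- Secondary outcome measures: "TNSS and RQLQs will be assessed at the beginning, middle, and end of treatment period", and again at follow-up weeks 4, 8 and 12. This gives five post-baseline assessments.
- The treatment group: "Post-intervention assessments will be conducted at the second and fourth week after the intervention".
- Statistical analysis: "A significance level of α= 0.05 will be considered statistically significant". Groups are compared by ANOVA and in pairs. The section does not say whether the ANOVA must be significant first, in what order the pairs are taken, or whether they are adjusted.
- Sample size: "The calculations were performed with α=0.05 and β=0.1, and the maximum sample size for each group was determined to be 33 cases". Two comparisons against blank control were sized (ARAT and non-specific) and neither is ranked first. ARAT vs non-specific was not sized.
- The title calls the trial exploratory, but the abstract's Discussion expects "evidence demonstrating the safety and efficacy of ARAT".

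**The concern.** With three arms and two comparison times, the text offers six TNSS tests and does not say which one decides the trial. A benefit over blank alone, or one seen only at the end of follow-up, could be reported as the primary result on the same footing as a benefit over non-specific points at the end of treatment.

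These results mean different things. Only ARAT vs non-specific addresses whether the chosen acupoints matter. ARAT vs blank also captures attention and the pressing itself, in an unblinded trial with a self-rated outcome. If the choice is made after the results are seen, 0.05 no longer describes the error rate of the reported finding.

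**Working it through.** **Inputs from the protocol article.** Three arms; 33 evaluable per arm; alpha 0.05 (taken as two-sided, since sidedness is not stated); comparison at end of treatment and end of follow-up; pilot TNSS before and after in Table 2. **Assumed, not given:** correlation of TNSS between the two times, 0.3 to 0.7; pre-post correlation, 0 to 0.5; normal outcomes.

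**Step 1, the plan's own figure.** 33 / 0.9 = 36.7, rounded up to 37 per arm, and 3 × 37 = 111, so the dropout step reproduces. With alpha 0.05 and 90% power, 33 per arm corresponds to a standardised difference of (1.960 + 1.282) × √(2/33) = 0.798 for one contrast at one time. Whether 33 follows from Table 2 is a separate question; here it serves only as the number per arm.

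**Step 2, number of tests.** 3 pairs × 2 times = 6. If they were independent, the chance of at least one false positive would be 1 − 0.95⁶ = 26.5%. They are not independent: pairs share arms, and the two times share patients. Simulation is therefore needed.

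**Step 3, simulation under no effect** (33 per arm, pairwise t tests at two-sided 0.05, 20,000 trials or more per setting). *Gated* means that pairs count only when the ANOVA at that time is significant.

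| Event | One time | Two times, correlation 0.3-0.7 |
|---|---|---|
| Any significant pair, ungated | 12% | 20-23% |
| Any significant pair, gated | 5% | 8.6-9.8% |
| ARAT better than either control, ungated | 4.5% | 7.6-8.7% |
| ARAT better than either control, gated | 2.1% | 3.6-3.9% |

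The reference for the last two rows is 2.5%: one contrast, one time, in ARAT's favour. The ratios are 7.6/2.5 = 3.0 to 8.7/2.5 = 3.5 ungated, and 3.6/2.5 = 1.4 to 3.9/2.5 = 1.6 gated. Independent repeat runs agree within about half a percentage point. Widening the correlation to 0-0.9 gives 16-23% and 7-10% for any pair, ungated and gated.

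**Step 4, after the fix.** With one time and a fixed sequence of contrasts, the chance of any false positive in the sequence is at most 5%, and the first test falsely favours ARAT 2.5% of the time.

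Power is taken from Table 2 with SD of change = √(s_pre² + s_post² − 2·r·s_pre·s_post). Mean falls are 9.7 − 5.1 = 4.6 (ARAT), 9.5 − 7.1 = 2.4 (non-specific) and 10.1 − 7.3 = 2.8 (blank). The differences are 4.6 − 2.8 = 1.8 and 4.6 − 2.4 = 2.2. At r = 0.25 the pooled SDs are 2.23 and 2.41.

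| Pre-post correlation r | ARAT vs blank | ARAT vs non-specific |
|---|---|---|
| 0 | 80% | 89% |
| 0.25 | 90% | 96% |
| 0.5 | 98% | 99% |

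On post-intervention scores alone (differences 2.2 and 2.0, pooled SDs 1.65 and 1.80), both contrasts exceed 99%.

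**Step 5, the alternative.** Bonferroni over six tests (0.05/6 = 0.0083) leaves about 73% power at 33 per arm for the difference of 0.798. Restoring 90% needs about 49 per arm: 49/0.9 = 54.4, so 55, and 3 × 55 = 165.

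**The case against.** Several counter-arguments have force.

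- *The 20-23% is not a rate of false efficacy claims.* This stands. A reader might infer a one-in-five chance of wrongly declaring that ARAT works. That figure also counts non-specific vs blank and results against ARAT. The rate for false results favouring ARAT is 7.6-8.7% ungated or 3.6-3.9% gated.
- *Silence on gating is not a statement that pairs are ungated or unadjusted.* This stands. ANOVA followed by pairs is a natural reading, and the post-hoc procedure may sit in an analysis plan that is not shown. Gating controls the three-arm part at one time (5%) but leaves 8.6-9.8% over two.
- *The Outcomes sentence is general.* Partly stands. It cannot apply literally to measures taken only at the beginning and end of treatment. TNSS, however, is assessed at both post-baseline times it names. The sentence does not specify significance tests at baseline, so none should be inferred.
- *The two assessment schedules do not really conflict.* Largely stands. Weeks 2 and 4 fit the middle and end of a 4-week treatment period, so the treatment-group wording is probably loose. It does not show that a second primary time is intended.
- *The trial is exploratory.* This lowers the severity. It does not remove the point, because the abstract expects efficacy to be demonstrated and the trial was sized at 90% power.

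A missing analysis plan does not answer the point about the primary time. The published text already commits to two comparison times and ranks neither, so a later plan would have to choose between them.

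**Conclusion.** The point holds in this form: the protocol names neither a primary time nor a primary contrast for TNSS and commits to between-arm comparison at two post-baseline times at 0.05. Either reading of the pairwise procedure inflates the error, by a factor of 3.0 to 3.5 (ungated) or 1.4 to 1.6 (gated) for a false result in ARAT's favour. The documents do not settle which reading applies.

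These figures rest on two-sided tests, 33 per arm and an assumed between-time correlation of 0.3 to 0.7. They do not cover all five post-baseline assessments, because the Outcomes section commits to only two comparison times. This should be fixed; it is not critical in a trial titled exploratory.

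**What to change.** In the Outcomes, Primary outcome measures and Statistical analysis sections, state:

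> Primary endpoint: change in TNSS from baseline to the end of the 4-week treatment period, adjusted for baseline TNSS. Tests in fixed sequence at two-sided 0.05: (1) ARAT vs blank; (2) ARAT vs non-specific, only if (1) is significant. A claim for the specific acupoints requires both. Non-specific vs blank and all other times are secondary and reported as estimates with 95% confidence intervals.

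In the treatment-group section, align the assessment times with the schedule under Secondary outcome measures. Recruitment has begun, so record the choice before outcome data are examined by arm.

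**Cost.** The sample size is unchanged. Non-specific vs blank and later-time results can no longer carry the primary claim. That is a real concession, since the former was one of the two contrasts used for sizing. The documents do not dictate this order; any order fixed in advance at one time holds 5%.

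On unadjusted change scores, power is about 80-98% for ARAT vs blank and 89-99% for ARAT vs non-specific. The figure above 99% for both applies only to post scores and should not be quoted for a change endpoint. Power for the claim that needs both cannot exceed the lower of the two and is at least their sum minus one: at r = 0, between 80 + 89 − 100 = 69% and 80%.

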#### Primary outcome measures

The primary outcome measure for this clinical trial will be TNSS. TNSS evaluates four nasal symptoms: nasal obstruction, running nose, sneezing, and nasal itch. Participants will self-assess and record the severity of their symptoms using a four-point scale (0 = no symptoms; 1 = mild symptoms; 2 = moderate symptoms; 3 = severe symptoms) [3, 28]. TNSS scores range from 0 to 12, , with lower scores indicating milder nasal symptoms. Previous studies [29, 30] have utilized the TNSS as an assessment tool.

